# The cost-effectiveness and cost-utility of at-home infrared temperature monitoring in reducing the incidence of foot ulcer recurrence in patients with diabetes (DIATEMP): study protocol for a randomized controlled trial

**DOI:** 10.1186/s13063-018-2890-2

**Published:** 2018-09-24

**Keywords:** Diabetes mellitus, Diabetic foot ulcer, Ulcer recurrence, Diabetic foot, Prevention, Home-monitoring, Foot temperature, Cost-effectiveness, Cost-utility

## Abstract

**Background:**

Home monitoring of foot temperatures in high-risk diabetes patients proves to be a promising approach for early recognition and treatment of pre-signs of ulceration, and thereby ulcer prevention. Despite previous studies demonstrating its efficacy, it is currently not widely applied in (Dutch) health care.

**Methods:**

In a multicenter, outcome-assessor-blinded, randomized controlled trial, 304 patients with diabetes mellitus types I or II, loss of protective sensation based on peripheral neuropathy, and a history of foot ulceration in the preceding 4 years or a diagnosis of Charcot neuro-osteoarthropathy will be included. Enhanced therapy will consist of usual care and additional at-home daily measurement of foot temperatures at six to eight predefined locations on the foot. If a contralateral foot temperature difference of > 2.2 °C is found on two consecutive days, the participant is instructed to contact their podiatrist for further foot diagnosis or treatment, and to reduce ambulatory activity by 50% until temperatures are normalized. Enhanced therapy will be compared to usual care. The primary outcomes are the cost (savings) per patient without a foot ulcer (i.e., cost-effectiveness) and per quality-adjusted life year gained (i.e., cost-utility). The primary clinical outcome in the study is the proportion of patients with foot ulcer recurrence on the plantar foot, apical surfaces of the toes, the interdigital spaces or medial and lateral forefoot surfaces during 18-month follow-up.

**Discussion:**

Confirmation of the efficacy of at-home foot temperature monitoring in ulcer prevention, together with assessing its usability, cost-effectiveness and cost-utility, could lead to implementation in Dutch health care, and in many settings across the world.

**Trial registration:**

Netherlands Trial Registration: NTR5403. Registered on 8 September 2015.

**Electronic supplementary material:**

The online version of this article (10.1186/s13063-018-2890-2) contains supplementary material, which is available to authorized users.

## Background

Despite many recent advances in medical therapies, the prevalence of diabetes mellitus and diabetes-related complications continues to increase. With a life-time prevalence of 19–34% [1], foot ulceration is one of the most common complications in people with diabetes. This frequently leads to hospitalization and lower-extremity amputation [2]. With an annual incidence rate of 2.2% and one million people with diabetes, approximately 22,000 ulcers develop in the Netherlands each year [3, 4]. Foot ulcers frequently become infected, cause great morbidity and have a negative impact on health-related quality of life and patient mobility [5–7]. Furthermore, mortality risk at 10 years is twice as high in patients who had a foot ulcer compared to those who have not [8]. Besides the patient and social burden of diabetic foot disease, foot ulcers cost €5000 to €17,000 per episode in specialized centers in Europe and place a large burden on the health care systems [9].

Recognizing the potential for severe morbidity and high treatment costs related to foot ulceration, many experts call for widespread establishment of preventative foot care programs for persons with diabetes [10–12]. The most common mechanism of foot ulceration involves a cumulative effect of repetitive trauma at pressure points on the foot over the course of several days that goes unrecognized because of the presence of neuropathy [1]. Guidelines therefore recommend proper patient education, identification and treatment of the diabetic foot at-risk, integrated foot care and protective pressure-relieving footwear [10, 13, 14]*.* Despite these guidelines, the incidence of foot ulcer recurrence remains very high: 40% in the first year and 60% in the first 3 years after healing of a foot ulcer [1]. Therefore, care providers and patients are in need of new adjunctive ways to prevent ulcer recurrence.

Stimulated by the need for innovation in foot ulcer prevention, at the beginning of this millennium, researchers developed the concept of at-home monitoring of foot temperatures as a preventative tool [15–17]. Foot ulcers are preceded by increased local skin temperature due to inflammation and enzymatic autolysis of tissue as a result of being ambulatory [16, 18]; the foot tends to locally heat up before it breaks down. These increased temperatures can easily be assessed by the patients themselves using some form of thermometry that measures skin temperature at predefined regions of the foot [16]. By monitoring these temperatures on a frequent basis (preferably daily), the patient can identify signs of inflammation and impending ulceration. Timely identification of these warning signs allows the patient or care provider to take action to decrease the inflammation before an ulcer develops; for example, by reducing ambulatory activity, and/ or providing (further) offloading of the specific regions with footwear, orthoses or felted foam. In three randomized controlled trials (RCTs), such at-home monitoring of the foot temperature was shown to be a highly effective tool in preventing foot ulcer recurrence in patients with diabetes [15–17].

Despite the demonstrated efficacy of at-home monitoring of foot temperature in these studies [15–17], the intervention is currently not widely applied in (Dutch) health care. This may be because the external validity of the findings of these studies has not been proven to date, as the studies were conducted by the same research group in one geographical location in the United States (US). Recently, another RCT that followed a similar study protocol and used the same infrared temperature device as the previous US studies was conducted in Norway [19]. They found no statistical difference in ulcer recurrence rate between patients who monitored their skin temperature at home and patients who did not. However, only 41 patients were included in this study and the follow-up time was only 1 year, which means that this study was underpowered and caution is needed in interpreting these findings [19]. Another reason for the limited implementation in daily foot care may be that the intervention involves the purchase of a thermometer, while it is unclear whether the costs are reimbursed or have to be covered by the patient. And when “hot-spots” occur, additional diagnosis and treatment may be needed, of which frequency, costs and reimbursement are all unknown. Furthermore, the daily assessment and recording of foot temperatures may be seen as cumbersome and a heavy load in a situation where patients already have to monitor many aspects of their disease (e.g., glucose monitoring, insulin application, medicine intake, frequent check-ups, footwear use, etc.). Additionally, the knowledge on diagnostic accuracy of foot temperature assessments (e.g., false-positive and false-negative outcomes) is limited. The aforementioned US studies [15–17] did not report false-positive or false-negative outcomes. Eight of the 21 intervention-group patients in the Norwegian RCT measured an increased skin temperature one or more times during that study, but only four of these patients contacted the study nurse, and none developed a foot ulcer [19]. Recently, Frykberg and colleagues showed that with the use of a plantar foot-temperature-monitoring mat, 97% of all non-traumatic diabetic foot ulcers that developed in a group of 132 patients with a history of foot ulceration could be identified before development of the ulcer through a temperature difference > 2.2 °C between similar spots on both feet [20]. However, a high false-positive rate was also found (57% of temperature differences of > 2.2 °C found were false alarms), and the variation of contralateral temperature differences in the group of patients that did not develop a foot ulcer was substantial: 2.81 °C (±1.42 °C). Similar high rates of false-positive outcomes were also described by Wijlens and colleagues [21]. When such incorrect observations are made, they can result either in over-diagnosis or over-treatment resulting in an additional burden for both the patient and the health care system. For these reasons, it is important that more knowledge is gained in different settings on the effectiveness, cost-effectiveness, cost-utility, and diagnostic accuracy of using at-home temperature monitoring in high-risk patients with diabetes.

The International Working Group on the Diabetic Foot (IWGDF) identified ulcer prevention as an area where data on the effectiveness of interventions is scarce and data on their cost-effectiveness is lacking [10–12]. A better understanding of how (recurrent) foot ulcers develop and how they can be prevented in a cost-effective way, has major relevance for the patient and health care. Therefore, we have designed the Diabetic Foot Temperature Trial (DIATEMP). DIATEMP aims to assess the effectiveness, cost-effectiveness and cost-utility of at-home infrared foot-temperature monitoring to reduce the incidence of foot ulcer recurrence in patients with diabetes mellitus.

## Methods

### Primary objective

To evaluate the effectiveness, cost-effectiveness and cost-utility of daily at-home infrared plantar foot temperature monitoring to reduce the incidence of foot ulcer recurrence in patients with diabetes mellitus.

### Hypothesis

We hypothesize that enhanced therapy, which includes at-home infrared temperature monitoring of the foot, results in a significantly lower proportion of patients with foot ulcer recurrence, is cost-effective and saves costs per quality-adjusted life years (QALYs) gained when compared to usual care. The hypothesis is based on superiority of enhanced therapy compared to usual care.

### Standard protocol items

The DIATEMP trial protocol was written in accordance with the Standard Protocol Items: Recommendations for Interventional Trials (SPIRIT). The SPIRIT 2013 Checklist has been included as Additional file 1.

### Study design

The study design is a multicenter, outcome-assessor-blinded, parallel-group RCT with two study arms:Enhanced therapy, including usual care as provided in the Netherlands and additional at-home daily plantar foot temperature monitoringUsual care as provided in the Netherlands

Patient recruitment takes place from seven university- or community-based hospitals with a multidisciplinary diabetic foot clinic in different regions throughout the Netherlands and from professional practices of podiatrists who participate in these multidisciplinary teams. Each diabetic foot clinic will operate as one of the study centers. Within each center, a physician and a podiatrist, both members of the diabetic foot team, will be involved. The participating hospitals are: Academic Medical Center (Amsterdam), VU Medical Center (Amsterdam), Ziekenhuisgroep Twente (Almelo), Maxima Medisch Centrum (Veldhoven), Maastricht University Medical Center (Maastricht), Reinier de Graaf Gasthuis (Delft), and Medisch Spectrum Twente (Enschede). Participants who consent to participate and who meet the inclusion and not the exclusion criteria will be randomized to the usual care or the enhanced therapy group. Each participant will be followed for 18 months or until a foot ulcer develops, after which the participant will be followed for the remainder of 18 months for the cost analysis only. The SPIRIT Figure (Fig. 1) shows an overview of the study design and the main procedures that participants will undergo during the course of the study.

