### Outcomes

The primary outcomes in this study are the cost (savings) per patient without a foot ulcer (i.e., cost-effectiveness) and per QALY gained (i.e., cost-utility). The primary clinical outcome is the proportion of participants with a recurrent foot ulcer on the plantar foot, apical surfaces of the toes, interdigital spaces or medial and lateral forefoot surfaces during 18-month follow-up. A foot ulcer is defined as a cutaneous erosion through the dermis without reference to time present [22, 23]. Endpoints in the study are either a foot ulcer, or 18 months of follow-up.

Secondary outcomes are the costs of therapy and of ulcer treatment, adherence to at-home foot temperature monitoring, and a multivariate risk score for ulcer recurrence.

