### Statistical analysis

Statistical analysis will be performed after the last follow-up visit of the last participant in the study, and will be conducted using SPSS statistical software (IBM Corporation, Armonk, NY, USA). All tests will assess group effects, will be two-sided, and use *P* < 0.05 as significance level. All comparisons between groups are based on both an intention-to-treat and a per-protocol analysis.

Effectiveness of the intervention will be assessed using chi-square analysis. A competing risk analysis will be done to assess the difference by time to ulcer recurrence, with unrelated death as the competing risk and absence of ulcer at 18 months as censored observation.

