### Economic evaluation

The economic evaluation will be performed as a cost-effectiveness analysis with the costs per prevented foot ulcer as the primary outcome. A cost-utility analysis will be performed with the costs per QALY as outcome. Both will be performed from a societal perspective. Considering the time horizon of 18 months, we will discount the effects and costs during the second year of follow-up. The Dutch Government recommends a discount rate of 4% for costs and 1.5% for effects [28].

Given the societal perspective, data will be collected on direct medical and non-medical costs as well as indirect non-medical costs. Direct medical costs include, for example, the costs of foot care, the thermometer and care provided by other health care professionals (general practitioner, medical specialist). Direct non-medical costs include, for example, out-of-pocket expenses by patients for travel to and from health care providers, private household assistance, and over-the-counter medication. Indirect non-medical costs reflect the costs of productivity loss due to sick leave from work or lower productivity while at work. Costs will be calculated as the product sum of resource volume data and their respective unit costs, as described in the Dutch manual for costing in health care research [29]. Costs associated with productivity loss will be based on the friction cost method, applying the actual mean friction period in the base year of the study. After price-indexing with general yearly consumer price indices, all costs will be expressed in euros for the base year 2015.

Incremental cost-effectiveness ratios will be calculated as the extra costs per additional patient without foot ulcer and the extra costs per QALY gained. To account for sampling variability, group differences will be assessed by calculating the 95% confidence intervals after correction for bias and using accelerated non-parametric bootstrapping. If enhanced therapy does not dominate usual care, results will be displayed graphically with cost-effectiveness acceptability curves for willingness to pay values up to €100,000.

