The measurement protocol in our trial was largely based on previous trials of Lavery and Armstrong and colleagues, in which six predefined regions of interest were measured: hallux, first, third, and fifth metatarsal heads, midfoot, and hindfoot [15–17]. Since many foot ulcers occur at the toes, and re-ulceration occurs mostly at the previous ulcer location [31], we added the option of measuring a maximum of two regions of interest in addition to the standard six, to provide a solution for previous foot ulcers or signs of pre-ulceration (e.g., abundant callus, subcutaneous hemorrhage or blister) being present at toes two to five. During the trial we noticed (blinded to group allocation) that ulcers did not develop at the midfoot or hindfoot. Therefore, in October 2017, we modified the six standard regions of interest to include the plantar surface of the second and third toes instead of the midfoot and hindfoot [20, 24]. For participants with a high risk of developing a foot ulcer at the midfoot or hindfoot, such as in midfoot Charcot deformity, this region would still be selected for temperature measurement as an additional region of interest.

A strength of this trial is that, in addition to assessing effectiveness in preventing foot ulcer recurrence, we assess cost-effectiveness and cost-utility of the procedure. These outcomes are important given the extra investment in measurement equipment and time of the health care professional and the patient in monitoring the foot. Another strength is that not just any foot ulcer, but only plantar foot ulcers and ulcers that develop at the apex of the toes, the interdigital spaces, and the lateral and medial forefoot are the primary clinical outcome. These locations are often subject to foot ulceration as a result of repetitive mechanical stress due to deformity present and rubbing of the toes. If inflammation occurs at these areas before foot ulceration develops, we anticipate that the temperature increase due to the inflammation is being measured at one of the measurement locations on the foot.

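### Clinical follow-up stops at a foot ulcer of any site, but the primary clinical outcome counts only listed sites, so a first ulcer elsewhere can hide a later qualifying one

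*Protocol article*

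**What the plan says.** **Stopping rule.** Study design sets the end of clinical follow-up: "Each participant will be followed for 18 months or until a foot ulcer develops". For the time that remains once an ulcer has occurred, the same sentence adds: "after which the participant will be followed for the remainder of 18 months for the cost analysis only". Outcomes repeats the rule: "Endpoints in the study are either a foot ulcer, or 18 months of follow-up". Neither statement of the rule names a site.

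**Definition.** The sentence just before the endpoint rule in Outcomes reads: "A foot ulcer is defined as a cutaneous erosion through the dermis without reference to time present". It fixes depth and duration and is silent on location.

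**Primary clinical outcome.** The event that Outcomes counts, as a proportion in each arm, is: "recurrent foot ulcer on the plantar foot, apical surfaces of the toes, interdigital spaces or medial and lateral forefoot surfaces during 18-month follow-up". The Abstract gives the same sites. The Discussion presents the restriction as deliberate and as a strength: "not just any foot ulcer, but only plantar foot ulcers and ulcers that develop at the apex of the toes", followed by the remaining listed sites.

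**Analysis.** Effectiveness is tested by chi-square, and the sample size section assumes that clinical outcome data from all included patients are assessed. The time-to-ulcer analysis is a competing-risk analysis "with unrelated death as the competing risk and absence of ulcer at 18 months as censored observation".

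**Economic effect.** Outcomes expresses cost-effectiveness per patient without a foot ulcer. Economic evaluation opens "with the costs per prevented foot ulcer as the primary outcome", then defines the ratio as extra cost per additional patient without a foot ulcer. Neither section says whether this means any site or the listed sites.

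**The concern.** The event that ends clinical follow-up is wider than the event being counted. Take a participant whose first ulcer is on the dorsum of the foot. The stopping rule is met, the primary outcome is not, and from then on the participant is kept for costs only. If a plantar ulcer follows before month 18, nothing in the article says that it counts.

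This participant fits neither planned analysis. In the chi-square on all included patients, the participant is classed as having no qualifying ulcer although follow-up for one stopped early. In the competing-risk analysis, the participant has neither died nor reached 18 months without an ulcer, and no rule for this exit is named.

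Two things are at stake. Qualifying events may be lost from a trial whose sample size has no margin. Also, sites, panel and analysts may apply the rule differently, so that the recorded proportion depends on local reading.

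**Working it through.** **1. The plan's own figure.** Inputs from the sample size section: 44% with usual care, 28.6% with enhanced therapy, two-sided α 0.05, power 80%. The allocation ratio is not stated; 1:1 is assumed. With pooled variance under the null and no continuity correction:

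n per arm = [1.960·√(2p̄(1−p̄)) + 0.842·√(p₁(1−p₁) + p₂(1−p₂))]² / (p₁−p₂)²

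p̄ = 0.363, 2p̄(1−p̄) = 0.4625, p₁(1−p₁) + p₂(1−p₂) = 0.4506, p₁−p₂ = 0.154.

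n = 3.602 / 0.02372 = 151.9, so 152 per arm and 304 in total. Power at 152 per arm is 80.0%. The stated 304 is reproduced.

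**2. Model for hidden events.** Assumptions, none of them from the article:
- 44% and 28.6% are the listed-site risks that full follow-up would show.
- Hazards are constant over 18 months.
- Non-listed ulcers occur independently of listed-site ulcers and with the same hazard in both arms.
- Follow-up for the primary outcome ends at the first ulcer of any site.

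Listed-site cumulative hazards: usual care −ln(0.56) = 0.5798; enhanced therapy −ln(0.714) = 0.3369.

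If a share s of the usual-care ulcer hazard is at non-listed sites, Hₙ = s/(1−s) × 0.5798, applied to both arms.

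Recorded primary proportion = H/(H+Hₙ) × [1 − exp(−(H+Hₙ))].

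Example, s = 20%: Hₙ = 0.1450. Usual care: 0.5798/0.7248 × (1 − e^−0.7248) = 41.2%. Enhanced therapy: 0.3369/0.4818 × (1 − e^−0.4818) = 26.7%.

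**3. Results at 152 per arm.**

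| Non-listed share (assumed) | Usual care | Enhanced | Difference (points) | Relative risk | Hidden events, usual care / enhanced | Power |
|---|---|---|---|---|---|---|
| 0% | 44.0% | 28.6% | 15.4 | 0.650 | 0 / 0 | 80.0% |
| 10% | 42.7% | 27.7% | 15.0 | 0.649 | 1.9 / 1.3 | 78.4% |
| 20% | 41.2% | 26.7% | 14.5 | 0.648 | 4.2 / 2.8 | 76.4% |
| 30% | 39.4% | 25.5% | 13.9 | 0.647 | 7.0 / 4.7 | 73.9% |

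Hidden events are 152 × (unmasked − recorded proportion).

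**4. Cross-check on another scale.** Setting the 18-month risk of a non-listed ulcer directly, equal in both arms, at 5%, 10%, 15% and 20% gives power of 78.7%, 77.4%, 76.0% and 74.5%. The picture is the same.

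**5. Unequal non-listed risk.** With a true listed-site risk of 44% in both arms and non-listed risks of 10% and 15%, the recorded proportions are 42.0% and 40.9%. That is a spurious difference of about 1 point.

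**The case against.** **The term may mean a listed-site ulcer.** In Outcomes, the endpoint sentence follows the site-restricted outcome, so "Endpoints in the study are either a foot ulcer, or 18 months of follow-up" could refer to the ulcer just described, and the definition between them does not address site either way. This reading is possible, but it is not stated, and the article does name sites elsewhere when it means them. If it is the intent, the text still needs to say so. What stands is that the article does not prove that later ulcers will be lost; that follows only from the literal reading.

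**Later ulcers may be known anyway.** The Ulceration procedure is not limited to the first ulcer, three-monthly calls ask all participants about any lesion, and cost questionnaires become monthly after an ulcer. This is true and makes the fix cheap. It does not override the cost-only rule. Retrieval of the 18-month ulcer outcome from records is described only for participants who withdraw.

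**Handling belongs in the analysis plan.** Coding a non-listed ulcer in the competing-risk model can be left to that plan. A stopping rule that conflicts with the stated outcome cannot, because ulcers never photographed or read by the panel cannot be recovered at analysis.

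**Stronger readings that the article does not support.**
- A reader might infer a seriously diluted treatment effect. Under the assumptions above the relative risk barely moves, and the absolute difference falls by at most 1.5 points.
- A reader might infer from "with the costs per prevented foot ulcer as the primary outcome" that an ulcer count is needed and cannot be formed. The same section defines the ratio per additional patient without a foot ulcer, so no count is needed and the phrase is probably loose wording.
- A reader might conclude that all-cause death should replace unrelated death as the competing event. That has no bearing on ulcer site and does not follow from this point.

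**Conclusion.** The mismatch is real and lies within the article: a stopping rule without a site restriction beside an outcome deliberately restricted by site. As written, a first ulcer at a non-listed site ends follow-up for the primary outcome, and the participant is then counted as having no event.

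Its consequence is probably modest: a power loss of about 2 to 6 percentage points over the assumed range. This rests on constant hazards, independence, equal non-listed risk in the two arms and a non-listed share that the article does not report. If a first ulcer raises the risk of another, more events would be hidden; the article gives no basis for sizing that. Unequal non-listed risk could add a small bias of about 1 point in the example.

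The sample size itself is correct, and the primary comparison is not invalidated. The point merits a clarifying amendment before analysis. Which ulcers the economic effect should count is the sponsor's choice; the article only needs to state it.

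**What to change.** In Study design and Outcomes, state that follow-up for the primary clinical outcome continues until the first panel-confirmed ulcer at a listed site, death or 18 months. Add that an ulcer elsewhere is recorded but does not end outcome follow-up. With that rule, the chi-square classification rests on the planned observation period, and a non-listed ulcer no longer creates an exit that the competing-risk analysis must handle.

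In Outcomes and Economic evaluation, state whether a patient without a foot ulcer means free of ulcers at any site or only at the listed sites.

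The cost is small. Telephone contacts are three-monthly, and cost follow-up already runs to month 18 after an ulcer. The addition is some outcome forms with photographs and some panel reads. No change to the sample size follows.
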